### FollowApp.Care platform

FollowApp.Care is an existing communications platform that collects patient-generated health data prior to or after a procedure in order to inform treatment care decisions, drive quality, and generate actionable performance reports. This patient-monitoring mobile phone platform has the ability to link with EHR systems without requiring an application program interface (API) and has already been linked to EHRs in the US as well as in Europe and Australia. FollowApp.Care can be deployed through any text message-enabled phone and configured to deliver language translations (e.g., Spanish) and generate aggregate reports at the patient, provider, practice, and organizational levels. FollowApp.Care meets all HIPAA requirements. Data are stored in a self-operated data center and is encrypted in transit and at rest. Different permission levels within the system ensure different levels of accessibility of the data. Using the platform requires few steps (Table 1); its functionality can be summarized as follows:Level 1 Providers - able to see their own patient responses & profilesLevel 2 Center Manager - able to see **all** patient responses and profiles within their assigned CenterLevel 3 Center SuperUser - able to see **all** patient responses and profiles of **all** Centers

**Table 1 Tab1:** FollowApp.Care at a Glance

Step 1 - FollowApp.Care automatically sends patients a customized post-procedure text containing a web-link to a personalized cloud-based survey	
Step 2 - Patients respond to the survey	
Step 3 - Survey results are relayed back to the FollowApp.Care system in real-time	
Step 4 - Patients in need are identified based on customizable notification settings. The provider is notified by email or text if an action is required, an alert is created within the FollowApp.Care platform prioritized by severity	
Step 5 - The provider is able to respond to each case to ensure patient needs are met	

### Instruments for data collection

Specific instruments include:mHealth questionnaires

The mHealth Questionnaire #1 includes questions about pre-procedural pain and patient demographics. The mHealth Questionnaire #2 includes questions about pain intensity and pain interference. Pain intensity questions are based on the PROMIS Item Bank v.1.0 – Pain Intensity Scale [39]. On days 1, 3, 5, 7, 14, and 21, patients are asked: “What is your level of pain right now?” On day 7, patients are also asked: “How intense was your pain at its worst since the procedure?” *Pain Interference* questions were taken from the validated Oral Health Impact Profile-14 (OHOP-14) [40] and the Revised American Pain Society Patient Outcome Questionnaire (APS-POQ-R) [41–43] questionnaires to focus attention on the small subset of activities (e.g., sleep) common to post-operative dental patients. If, on days 14 and 21, patients answer the pain intensity question (“What is your level of pain right now?”) as positive (> 0), they will also be asked the six pain interference questions. The mHealth Questionnaire #2 will also collect the following additional information: type and frequency of pain-relief medications taken and the presence of concurrent symptoms such as bleeding, visible swelling, suppuration (pus), and/or fever. The mHealth Questionnaire #3 includes questions from the 2nd mHealth questionnaire and questions about patient pain management satisfaction (see Additional file 1: Appendix 1).2.System Usability Scale (SUS) questionnaire

*FollowApp.Care usability as perceived by patients will be measured* by the system usability scale (SUS) [44–46] questionnaire to measure the usefulness and ease of use of the FollowApp.Care platform. The validated SUS is a simple questionnaire that uses a ten-item attitude Likert scale, giving a global view of subjective usability assessments (see Additional file 2: Appendix 2).3.Unified Theory of Acceptance and Use of Technology (UTAUT)

*Practitioner acceptance* with the FollowApp.Care platform will be measured by the Unified Theory of Acceptance and Use of Technology (UTAUT) [47] questionnaire to evaluate FollowApp.Care usage, perceived usefulness, ease of use, and impact on clinical workload. The UTAUT model measures the relationships between use intention and two independent constructs – performance expectancy and effort expectancy. The UTAUT model integrates eight major theories and has been tested and validated using large real-world data sets (see Additional file 3: Appendix 3).4.electronic Case Report Form (eCRF)

Two eCRFs record practitioner information (practitioner characteristics) and patient information (patient demographics, diagnoses and procedures, pain levels, pain management plan, and complications) at Days 0 & 21 (see also Appendix 3).5.Debriefing/interview

Telephone debriefing/interviews with purposefully selected practitioners will be conducted to qualitatively evaluate their experiences with using FollowApp.Care for managing their patients’ post-operative pain, including its impact on their clinic workload and workflow patterns, and satisfaction with the effectiveness of pain management.

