## Hypotheses

The study includes the following hypotheses:

### Hypothesis 1

There is a significant difference in pain intensity measured over time and the dental procedure groupings after adjusting for pain management strategies and other complications. More specifically, are their significant variations in pain intensity due to different treatments after adjusting for:pain management strategy (e.g., pain medications used, adherence to pain management strategy, the usage of non-medicine methods for pain)other complications

### Hypothesis 2

There is a significant difference in pain interference measured over time and the dental procedure groupings, after adjusting for pain management strategies and other complications. More specifically, are their significant variations in pain interference due to different treatments after adjusting for:pain management strategy (e.g., pain medications used, adherence to pain management strategy, the usage of non-medicine methods for pain)other complications

### Hypothesis 3

There is a significant difference in patient satisfaction measured at the end of the 7-day period and dental procedure groupings, after adjusting for pain management strategies and other complications. More specifically, are their significant variations in patient satisfaction due to different treatments after adjusting for:pain management strategy (e.g., pain medications used, adherence to pain management strategy, the usage of non-medicine methods for pain)other complications.

### Hypothesis 4

Reported technology acceptance metrics; performance expectancy (PE), effort expectancy (EE), social influence (SI), and behavioral intention (BI) will be consistent with high acceptance of the FollowApp.Care platform.

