## Design and methods

### Study design

POPS is a longitudinal, prospective cohort study that will be conducted with practitioners and their patients undergoing potentially painful dental procedures. Data about baseline pain intensity and patient demographics will be collected prior to the procedure. The patients will receive push notifications through text messages via the FollowApp.Care platform on their mobile devices which asks them to comprehensively record their pain experience at designated time intervals on days 1, 3, 5, 7, 14, and 21 following their procedure. At the end of the 1st week (day 7), they will be asked to report their satisfaction with their post-operative pain management. On Day 23, after the procedure, they will be requested to complete a questionnaire to measure the platform’s usefulness and ease of use. All participating practitioners will be invited to complete a questionnaire to assess the platform’s perceived usefulness and ease of use. A subgroup of practitioners will also be invited to participate in debriefing/interviews to qualitatively evaluate their experiences with using FollowApp.Care for managing their patients’ post-op pain.

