### Study outcome measures

This study has two primary outcomes, which reflect 1) pain experience and 2) patient pain management satisfaction. *Pain experience* refers to both pain intensity and pain interference. *Pain intensity* is an assessment of how much a patient hurts. The response categories range from “No pain” to “Very severe” on a 10-point Likert scale [39]. Pain intensity is a relatively homogeneous dimension, and most measures of pain intensity tend to be interchangeable. It was selected because of its relevance to dental patients and practitioners, applicability to all conditions, including acute postoperative dental pain for assessing symptoms, ease of administration, and the relative accuracy with which most adult patients gauge pain. *Pain interference* refers to the extent to which patients have experienced interferences that have prevented them from activities of daily living (ADL), falling asleep, and staying asleep. The response categories range from “Does not interfere” to “Completely interferes” on a 10-point Likert scale. *Patient pain management satisfaction* refers to the level with which patients are satisfied with the overall pain management following their procedure and shared pain management strategies. The response categories range from “Extremely dissatisfied” to “Extremely satisfied” on a 10-point Likert scale. Additionally, it encompasses whether the patient participated in the decision-making regarding their treatment. The response categories range from “Not at All” to “Very Much So” on a 10-point Likert scale.

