Secondary outcomes include 1) *Analgesic medications used by patients* that are reported through FollowApp.Care, frequency and dose prescribed captured through the eCRF completed by the practitioners; adherence to pain medications prescribed collected from the patient-reported data through FollowApp.Care, 2) *Concordance with pain management strategy* as recommended by the practitioner (reported on the eCRF) and reported by the patient. The pain management strategy of each practitioner will be captured on the eCRF, and the mHealth questionnaire will capture the corresponding patient adherence. 3) *Other pain management strategies* used by patients (post-op pain management strategies including usage of other pain management strategies, such as non-medicine methods for pain relief), 4) *Practitioner acceptance* of the platform (usage, perceived usefulness, ease of use, and impact on clinical workload), 5) *Patient perceived usability* with the platform (usefulness and ease of use of the platform), and 6) *Other complications* related to immediate postoperative complications (bleeding and increased swelling).

Other covariates are *Baseline pain intensity, Patient demographic* variables, *Type of procedure* (CDT), P*ractitioner demographic* variables, *Practitioner specialty, Practitioner years in practice (*the year of graduation from dental school), and Practitioner assessment of *expected pain intensity.*

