### Study activities and data collection

Participating patients will be encouraged to complete the mHealth Questionnaire #1 prior to the procedure. Baseline pain intensity and patient demographic variables will be collected through the welcome message. *Type of procedure* (CDT) will be collected through the eCRF. *Practitioner demographic* variables, *specialty, and years in practice* will be collected through the practitioner’s enrollment questionnaire (EQ). This information is already available in the practitioner database, and enrolled practitioners will be asked to update their EQ before the study. *Practitioner years in practice* will be collected through the practitioner’s enrollment questionnaire (EQ).

Upon completing their procedures, all enrolled patients will receive post-operative instructions and guidance according to the provider’s standard practice. Additionally, all enrolled patients will receive guidance about FollowApp.Care. At the end of each day, the research staff will retrieve the new patient profiles from FollowApp.Care and check the patient contact information for completeness. The patients will receive text/email notifications at pre-determined time intervals (e.g., 9 am) on Days 1,3,5,7,14, and 21 and will be prompted to complete the corresponding mHealth Questionnaire (Table 2). An additional comment/chat feature will enable patients to securely communicate more information to their dental care team through the FollowApp.Care system, when needed. All patients will receive usual clinical care and can contact their provider/clinic by phone/in person if they so desire. Practitioner assessment of *expected pain intensity* will be collected through the eCRF.

**Table 2 Tab2:** Overview of the instruments

Instrument	Completion Time	Content	Completed by
mHealth Questionnaire #1	Day 0 (pre-procedure)	- Pre-procedural pain - Patient demographics	Patients
mHealth Questionnaire #2	Days 1, 3, 5 and 14 and 21	- Pain intensity levels, medications used, bleeding, and swelling - Pain interference (if having pain on 14 and 21)	Patients
mHealth Questionnaire #3	Day 7	-Pain intensity levels, medications used, swelling -Pain interference -Satisfaction with pain management treatment	Patients
System Usability Scale (SUS) Questionnaire	Day 23	Patients’ perceptions of the usability of the FollowApp.Care user interface	Patients

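### Pain interference, a primary-outcome component compared across non-randomised procedure groupings, has no described pre-procedure measure, so interference already present on Day 0 cannot be adjusted for directly

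*Protocol article*

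**What the plan says.** Three places in the protocol article describe what patients report before the procedure, and they agree. Study design says: "Data about baseline pain intensity and patient demographics will be collected prior to the procedure". Instruments for data collection says: "The mHealth Questionnaire #1 includes questions about pre-procedural pain and patient demographics". Table 2, under Study activities and data collection, gives the content of Questionnaire #1 as "Pre-procedural pain - Patient demographics".

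Study outcome measures states that pain experience, a primary outcome, "refers to both pain intensity and pain interference". Hypothesis 2 reads: "There is a significant difference in pain interference measured over time and the dental procedure groupings". It goes on to ask about variation due to the different treatments, after adjustment for pain management strategy and other complications.

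Interference, medication use and symptoms appear only in the post-procedure questionnaires. The symptoms asked about are "the presence of concurrent symptoms such as bleeding, visible swelling, suppuration (pus), and/or fever". The corresponding secondary outcome, other complications, is "related to immediate postoperative complications (bleeding and increased swelling".

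There is a second Day 0 source. The practitioner's eCRF covers "patient demographics, diagnoses and procedures, pain levels, pain management plan, and complications) at Days 0 & 21".

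Study outcome measures lists baseline pain intensity among the covariates. Statistical analysis then lists the fixed effects as time, treatment type, age, gender, race/ethnicity, medications and non-medication methods. Baseline pain is not on that list, and neither section mentions baseline interference.

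**The concern.** The eligible procedures span endodontics, periodontics, oral surgery and implants, and the patient's condition decides which one is done. Patients may therefore differ in disturbed sleep or daily activity before anyone has treated them. If some of that carries into the first post-operative days, a contrast in interference between groupings mixes what the procedure caused with what the patient brought. The article names this threat itself, under Statistical analysis and again under Limitation, and offers regression adjustment as the remedy. Direct adjustment requires the variable to have been measured. For intensity the study collects a baseline value; for interference, none is described. This is a matter of what is collected, so it cannot be left to an analysis plan.

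A lesser form of the same gap affects two patient-reported items. The complication outcome speaks of increased swelling, but the patient item asks whether visible swelling is present, and no patient-reported Day 0 value is described from which to judge an increase. Analgesic use by the patient is likewise first described after the procedure. Complications and pain medication also serve as adjusters in Hypotheses 1 to 3, so a presenting symptom read as a complication would enter those models too.

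**Working it through.** **What is measured when, as the article describes it**

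| Quantity | Patient, Day 0 | Practitioner eCRF, Day 0 | Patient, after the procedure |
|---|---|---|---|
| Pain intensity | yes | pain levels | yes |
| Pain interference | not described | not listed | yes (Days 14 and 21 only if pain is above 0) |
| Swelling, bleeding, pus, fever | not described | diagnoses and complications; may cover some | yes |
| Analgesic use by the patient | not described | not listed (the pain management plan is) | yes |

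The interference row is the one with no Day 0 source of any kind. The exact items sit in appendices that are not shown, but the three descriptions of the pre-procedure form all give the same two topics.

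**The plan's own figures.** From Sample size: 3147 × (1 − 0.40) = 1888.2, which reproduces the stated 1888. Also 150 × 21 = 3150, close to the stated 3147. The 80% power cannot be reproduced, because no mean, SD, within-patient correlation or number of groups is given. The point here depends on none of these figures.

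**Illustration of size, on assumed values.** Work in SD units. Let D be the difference between two groupings at Day 0, taken as equal for pain and interference. Let b be the carry-over slope from Day 0 interference to post-operative interference, and r the within-group correlation of Day 0 pain with Day 0 interference. Then:

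- bias without any baseline adjustment = b × D
- bias left after adjusting for baseline pain only = b × (D − r × D) = b × D × (1 − r)

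Assumed ranges: b from 0.2 to 0.6, D from 0.25 to 0.5, r from 0.3 to 0.7.

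- Unadjusted, lowest: 0.2 × 0.25 = 0.05 SD
- Unadjusted, highest: 0.6 × 0.5 = 0.30 SD
- After baseline pain, lowest: 0.05 × (1 − 0.7) = 0.015 SD
- After baseline pain, highest: 0.30 × (1 − 0.3) = 0.21 SD

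**A yardstick.** Take the 1888 patients in equal groups, two-sided α = 0.05 and 80% power, ignoring clustering and repeated measures. The detectable difference between two groups is (1.960 + 0.842) × √(2/n).

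- Two groups, n = 1888/2 = 944: 0.129 SD
- Four groups, n = 1888/4 = 472: 0.182 SD

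The number and equality of groups and the two-sided test are assumptions; the article states none of them. The SD scale is a convenience, since the planned models are Poisson and report relative risks.

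**The case against.** A reader might infer more than this: that pre-existing interference and symptoms are simply counted as post-operative and cannot be adjusted for at all. The documents do not support that. The practitioner records diagnoses and complications on Day 0, and a diagnosis could identify many patients treated for an infected or painful tooth. Baseline pain intensity is collected and named as a covariate, and it should carry part of the information in baseline interference. The complication outcome is worded as increased swelling, not swelling as such, and does not name pus or fever. Whether Day 0 complications on the eCRF means presenting symptoms cannot be settled without the appendix. The symptom part of the point is therefore limited to what patients report, and the interference part to direct adjustment.

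Two further objections have some force. The primary objective is largely descriptive, and the interference patients have after each type of procedure is a valid description without a baseline. That does not cover Hypothesis 2, which asks about differences due to treatment. Also, the protocol values short forms, only encourages completion of Questionnaire #1 before the procedure, and already assumes 40% missing data, so a longer form could lower completion of the baseline pain score itself. That is a real cost and belongs in the decision.

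The eCRF does not answer the main point, because neither interference nor current analgesic use is among its listed contents. The pain proxy is also less secure than it looks: if the models are fitted with the fixed effects as listed, baseline pain is not in them.

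**Conclusion.** The point stands for interference. A component of a primary outcome is compared across non-randomised groupings with no described pre-procedure measure, and what is available instead is partial: a baseline pain score missing from the listed model terms, and Day 0 diagnoses. For symptoms and medication it stands only in the narrower sense that swelling and analgesic use have no described patient-reported value at Day 0.

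The size of the residual bias cannot be derived from the documents, which give no Day 0 distribution by procedure and no correlations. On the assumed values it runs from 0.015 SD, which is negligible, to 0.21 SD, which is about the size of a detectable effect (0.13 to 0.18 SD). It would be wrong to read this as evidence that Hypothesis 2 will be materially biased. What can be said is that the study, as described, has no direct means of telling which end of the range applies. This is a worthwhile and inexpensive improvement to a primary comparison, not a flaw that invalidates the study.

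**What to change.** Add the six existing interference items to mHealth Questionnaire #1. If form length allows, add the visible swelling and current analgesic items as well. In the interference model, include Day 0 interference together with baseline pain intensity as covariates, and reconcile the fixed-effects list under Statistical analysis with the covariates under Study outcome measures, so that baseline pain is in the model. Use the Day 0 eCRF diagnoses and complications to separate pre-existing from new symptoms, and state whether the eCRF's Day 0 complications field covers presenting symptoms.

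The items already exist on the platform, which the article says can collect data before a procedure. The cost is a protocol amendment and a longer pre-procedure form, with possibly lower completion; for that reason the interference items come first and the others are optional. Patients already enrolled keep the pain-only baseline, so the analysis would need to say how the two sets are handled.

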### Study activities and data collection

Participating patients will be encouraged to complete the mHealth Questionnaire #1 prior to the procedure. Baseline pain intensity and patient demographic variables will be collected through the welcome message. *Type of procedure* (CDT) will be collected through the eCRF. *Practitioner demographic* variables, *specialty, and years in practice* will be collected through the practitioner’s enrollment questionnaire (EQ). This information is already available in the practitioner database, and enrolled practitioners will be asked to update their EQ before the study. *Practitioner years in practice* will be collected through the practitioner’s enrollment questionnaire (EQ).

Upon completing their procedures, all enrolled patients will receive post-operative instructions and guidance according to the provider’s standard practice. Additionally, all enrolled patients will receive guidance about FollowApp.Care. At the end of each day, the research staff will retrieve the new patient profiles from FollowApp.Care and check the patient contact information for completeness. The patients will receive text/email notifications at pre-determined time intervals (e.g., 9 am) on Days 1,3,5,7,14, and 21 and will be prompted to complete the corresponding mHealth Questionnaire (Table 2). An additional comment/chat feature will enable patients to securely communicate more information to their dental care team through the FollowApp.Care system, when needed. All patients will receive usual clinical care and can contact their provider/clinic by phone/in person if they so desire. Practitioner assessment of *expected pain intensity* will be collected through the eCRF.

**Table 2 Tab2:** Overview of the instruments

Instrument	Completion Time	Content	Completed by
mHealth Questionnaire #1	Day 0 (pre-procedure)	- Pre-procedural pain - Patient demographics	Patients
mHealth Questionnaire #2	Days 1, 3, 5 and 14 and 21	- Pain intensity levels, medications used, bleeding, and swelling - Pain interference (if having pain on 14 and 21)	Patients
mHealth Questionnaire #3	Day 7	-Pain intensity levels, medications used, swelling -Pain interference -Satisfaction with pain management treatment	Patients
System Usability Scale (SUS) Questionnaire	Day 23	Patients’ perceptions of the usability of the FollowApp.Care user interface	Patients
UTAUT Questionnaire	After practitioner completes enrollment of all their patients	Explores four core constructs: performance expectancy, effort expectancy, social influence, and facilitating conditions as direct determinants of behavioral intention and behavior	Practitioners
electronic Case Report Form (eCRF)	Days 0 and 21	Two eCRFs: - Practitioner info (practitioner characteristics) - Patient info (diagnoses and procedures, pain levels, pain management plan, and complications)	Practitioners
Debriefing/interview	After practitioner completes enrollment of all their patients	Practitioners’ experiences with using FollowApp.Care for managing their patients’ post-op pain.	Practitioners

Patients will also be asked to evaluate the usability of the FollowApp.Care system by completing the 10-item, System Usability Scale survey and providers the UTAUT questionnaire. Once the patient component of the study has been concluded, we will conduct telephone interviews with providers to qualitatively evaluate their experiences with using FollowApp.Care for managing their patients’ post-operative pain, including its impact on their clinic workload, workflow patterns, and satisfaction with the effectiveness of pain management.

See Table 3 for an overview of study activities.

**Table 3 Tab3:** Study activities

Task	Description of implementation/operationalization
1. Network Site Selection	We anticipate that all Network practitioners stratified by state, urban/rural, and practice size, will be eligible to participate. We will work with the Network coordinators to assure all sites are informed of the study protocol and the opportunity to participate.
2. Practitioner Recruitment and training	The Network site coordinators will use established protocols to recruit practitioners. The study team will work with the coordinators and the Network Communications Director to assure the dissemination of the study opportunity. The study team will provide the coordinators with all online training materials. Coordinators may decide to add an in-person training component. Study personnel will be available remotely via video conference/phone calls to support all training efforts.
3. Patient screening and enrollment	Each participating office will decide if practitioners or office staff will screen/enroll patients in the study. The office staff who enroll patients will need to have successfully completed appropriate training. Each participating office will maintain a log of screened and enrolled subjects. On a weekly basis, office staff will record their summary screening/enrollment information in the electronic data capture (EDC) system. Practitioners will enroll patients via a consecutive process that best suits their practice situation, i.e., they will approach any patient who may meet the inclusion criteria during the days and/or times when the office is participating in research activities.
4. FollowApp.Care platform activation	Enrolled practitioners will individually be able to request their FollowApp.Care notification preferences, for example, they can choose to receive notifications by email or text. Notifications will be sent to practitioners based on predefined thresholds defined in the manual of procedures (MOP).
5. Patient evaluation (Usability questionnaire)	Patients will complete a Usability survey (SUS) on day 23 using the FollowApp.Care platform.
6. Practitioner evaluation (debriefing/interview session and UTAUT questionnaire)	Once the patient component of the study has been concluded, we will administer the UTAUT Questionnaire to all participating practitioners to assess their perceived usefulness and perceived ease of use of FollowApp.Care as predictors of their usage behavior. Thereafter, we will conduct virtual debriefing/interviews with up to 45 purposefully selected practitioners to qualitatively evaluate their experiences with using FollowApp.Care for managing their patients’ post-op pain. These debriefing/interview discussions will be audiotaped and transcribed for analysis.

